### Treatment as usual

Sites that are randomised to the control group deliver the CST as usual. This can vary between centres and has the variability to change over time. The trial examines the additional effects of the outreach support and long-term effect in practice.

### Intervention

The outreach support options are identical to those in the training and monitoring study, with one difference: to emulate CST in practice, staff members identify the local supervisor, and if this is not possible, it is recorded accordingly. All the staff members randomised to receive outreach support are encouraged to use all the options available to them, but they are not compulsory. The staff member is monitored to measure their usage of the outreach support options.

### Primary outcome measure

The primary outcome is identical to the TROU trial. However, due to the nature of the recruitment, in that people are being recruited who have previously purchased the ‘Making a difference’ manual or attended CST training, it will be dependent on people’s interest in taking part in the research. As a minimum of one staff member can participate per centre; between 40 and 120 centres are required to recruit 120 staff members. This figure also accounts for a 15% attrition rate.

### Secondary outcome measures

The secondary outcome measures are identical to those in the TROU trial.

### Consent

Informed consent is gained from each staff member and a member of management, and is identical to the training and outreach trial. Ethical approval was granted June 2011 by East London REC 3.

### Blinding

The procedure for blinding is identical to the TROU trial.

### Analyses

#### *Training and outreach trial & Monitoring and outreach trial*

A combined analysis making use of the results from the training and outreach trial (120 participants) and the monitoring and outreach trial (120 participants) will be carried out. The primary outcome will be the mean number of CST sessions offered per centre assuming the intra-cluster correlation p to be 0.05. At the 6-month primary end point based on 240 staff members (120 outreach vs. 120 control) in the outreach group, the mean number of sessions offered is estimated to be 16 (SD 10) and in the control group the mean number of sessions offered is expected to be 12 (SD 10). Setting *p* at 0.05, power at 0.8, with the effect size at 0.4, then 200 participants would be required to demonstrate a difference between the groups.

Using all the participants recruited across both trials (TROU and MONO), a four-group comparison will also be made. This will compare training and outreach support, training and no outreach support, manual only and outreach, and manual only and no outreach support. This will determine if there are differences between these groups at 6 and 12 months.

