### Training and outreach trial (TROU)

The design is a pragmatic, multi-centre, single-blind, two treatment arm, randomised controlled trial. All participants receive the training package as treatment as usual (TAU) consisting of the 1-day CST training, training DVD, CST manual and maintenance CST manual. Participants in the intervention group also receive outreach support (local coordinator, email support and online forum). The sample is dementia care staff from specialist and non-specialist dementia care settings. The staff are cluster randomised according to place of work, before the training day, to receive outreach support or not. Each staff member completes three questionnaires, the first before the training day and at 6 and 12 months thereafter (Figure 1).

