### Participants

Staff members are screened to ensure they meet the inclusion criteria: (1) adequate written and spoken English, (2) able to complete online assessments at three different time points, (3) have at least two other team members with whom to run groups, (4) agreement from their management to have 2 h set aside per week to run the CST groups and 1 h following on from this for the 24-week maintenance CST programme, and (5) are able to provide between five to eight people with mild to moderate dementia who are willing to participate and meet the inclusion criteria (described in the observational arm). A minimum of three staff members is recruited per centre for logistical reasons of being able to consistently run the groups. Up to 40 centres are needed to be able to recruit the 120 staff members required for the trial. Working on the premise of a 15% attrition rate, the sample size will provide sufficient numbers for the staff training outreach support/no outreach support to estimate effect size and the feasibility of the trial. The attrition rate is an estimation based on previous research conducted in CST [12].

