### Primary outcome measure

The primary outcome measure is number of CST and maintenance CST sessions run in the centre by the follow-up at 31 weeks. This is recorded using the monitoring progress form located in the ‘Making a difference’ manual [14], which includes who was in attendance, level of interest, communication, enjoyment and mood, on a rating scale 1–5. This measure is being completed at the end of each session from baseline to 31 weeks (inclusive of maintenance CST), until the maintenance CST groups have been completed or until the groups have been discontinued.

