### Monitoring and outreach trial (MONOU)

The design is a pragmatic, multi-centre, single-blind phase IV trial. Participants are staff members from centres that have previously purchased the CST ‘Making a difference’ manual or attended a CST training course. The staff members are currently in possession of the CST manual or attended CST training. In addition to this, they all receive the maintenance CST manual and DVD. It is recorded whether participants have the manual only or manual and training. Centres are cluster randomised into outreach support or no outreach support (Figure 2). The time points for completing the questionnaire are the same as the training and outreach trial. However, they also complete a retrospective questionnaire on their use of CST in practice prior to the research.

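### The stated 200 participants ignores the intra-cluster correlation the plan says it assumes, and the primary outcome is one count per centre, so 80 to 160 centres give about 42% to 71% power if SD 10 is between centres

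*Protocol article*

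**What the plan says.** The outcome is defined in the protocol article under Primary outcome measure of the training and outreach trial (TROU): "The primary outcome measure is number of CST and maintenance CST sessions run in the centre by the follow-up at 31 weeks". The monitoring and outreach trial (MONOU) uses the same outcome.

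Both trials randomise centres. For TROU: "The staff are cluster randomised according to place of work". For MONOU: "Centres are cluster randomised into outreach support or no outreach support".

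The sample size is set for the two trials combined, in the Analyses section. It restates the outcome and names a correlation: "The primary outcome will be the mean number of CST sessions offered per centre assuming the intra-cluster correlation p to be 0.05". It expects 16 sessions (SD 10) with outreach and 12 (SD 10) without, on 240 staff members, 120 per arm. With significance set "at 0.05, power at 0.8, with the effect size at 0.4, then 200 participants would be required".

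The number of centres is given separately. For TROU: "Up to 40 centres are needed to be able to recruit the 120 staff members required for the trial". For MONOU, where a centre may contribute a single staff member: "between 40 and 120 centres are required to recruit 120 staff members".

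**The concern.** The paragraph mixes two units. The outcome belongs to the centre, but the required number is in staff. The intra-cluster correlation describes how alike staff within a centre are on a quantity that each of them has separately. A centre's session count is not such a quantity, because three colleagues at one centre have the same count and the second and third add no information on it. The number of centres therefore determines the power of the primary comparison, and fewer centres than staff are planned.

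The correlation also appears to have been named and then not used. If so, the required number is not the one the paragraph's own assumptions produce, whichever unit is meant.

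At stake is how the main result is read. The Discussion expects definitive evidence. If power is well below 80%, a real four-session benefit could be missed and the null result taken to mean that outreach does not work.

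**Working it through.** **Inputs.** Means 16 and 12, SD 10, alpha 0.05, power 0.8, 240 staff (Analyses); 1:1 allocation (Randomisation); at least three staff per TROU centre and up to 40 centres (TROU Participants); 40 to 120 MONOU centres (MONOU Primary outcome measure); 15% attrition (both trials). The protocol does not say whether the test is one- or two-sided; two-sided is used because it reproduces the stated number.

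**Step 1: reproduce the plan's figure.** Effect size d = (16 − 12)/10 = 0.4. Normal approximation: n per arm = 2 × (1.960 + 0.842)² / 0.4² = 98.1, rounded up to 99, total 198. The t-test needs 99.08 per arm, rounded up to 100, total 200. This is the stated number, with independent observations. A one-sided test gives 78 per arm, total 156, which does not match.

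**Step 2: was the correlation applied?** Design effect = 1 + (m − 1) × ICC. With m = 3 and ICC 0.05 it is 1 + 2 × 0.05 = 1.10, and 200 × 1.10 = 220. The plan's 200 corresponds to a design effect of 1.

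**Step 3: count the independent units.** 40 + 40 = 80 centres, up to 40 + 120 = 160. The design effect gives the same answer: staff of one centre share one value, so the ICC of this outcome is 1 and the design effect at m = 3 is 3. Then 240/3 = 80 units; with single-staff MONOU centres, 120/3 + 120 = 160.

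**Step 4: power with the centre as unit.** This takes SD 10 as the SD of counts between centres. Normal approximation: power = Φ(0.4 × √(C/4) − 1.960), where C is the total number of centres.

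| Centres | 0.4 × √(C/4) | Power, normal | Power, t-test |
|---|---|---|---|
| 80 | 1.789 | 43.2% | 42.4% |
| 120 | 2.191 | 59.1% | 58.4% |
| 160 | 2.530 | 71.6% | 71.0% |
| 200 | 2.828 | 80.7% | 80.4% |

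The difference detectable with 80% power (t-test, SD 10) is 6.34 sessions with 80 centres and 4.46 with 160, against the 4 planned for.

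**Step 5: the staff-level reading.** Suppose each staff member had a separate outcome with SD 10 and ICC 0.05. After 15% attrition, 240 × 0.85 = 204 staff remain.
- Three staff in every centre: 204/1.10 = 185 effective, power 77%.
- Three per TROU centre and one per MONOU centre: 102/1.10 + 102 = 195 effective, power about 79%.

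**The case against.** The strongest reply is that the paragraph may be meant at staff level. It gives the means and SD on 240 staff members beside a correlation that has meaning only for a staff-level quantity, and it does not say which unit the SD belongs to. On that reading the plan gives 77% to 79%, close to the stated 80%. This stands as far as it goes: the large shortfall depends on SD 10 being between centres. But the staff-level reading contradicts the outcome definition in two sections, and even there the stated correlation was left out of the 200.

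Three stronger readings are tempting and are not supported.
- A reader might infer that true power is 42% to 71% without condition. The SD condition applies, and the ends are not strict bounds. TROU may have fewer than 40 centres, so 42% is not a floor; 71% requires exactly one staff member in every MONOU centre.
- A reader might apply the 15% attrition to centres and lower the range further. The protocol ties that rate to staff numbers, and losing one of three colleagues need not lose the centre's count.
- A reader might infer that the analysis will enter 240 staff rows and give standard errors that are too small. The protocol does not say so; the 0.05 is a planning assumption, and the analysis model may be set out in a document not shown.

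The MONOU Randomisation section also describes dividing centres into two matched clusters that are then randomised. If centres are allocated as blocks and not one by one, the number of independently randomised units could differ from the number of centres. The text does not settle this.

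**Conclusion.** The point holds as an error of statement. The 200 participants is the figure for independent observations, the correlation of 0.05 was not applied, and it does not fit a primary outcome with one count per randomised centre.

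The size depends on the unit of the SD. If it is the between-centre SD, as the per-centre outcome implies, the planned centres give power of about 42% (80), 58% (120) and 71% (160). Reaching 80% takes about 200 centres, beyond the planned maximum of 160. If SD and correlation are at staff level, the shortfall is only a few percentage points. The centre-level reading is preferred because it follows the protocol's own outcome definition and unit of randomisation. All figures assume a two-sided test at 0.05 and equal allocation; the centre-level figures also assume that each centre is allocated independently and supplies a count.

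**What to change.** In the Analyses section for the two outreach trials:
1. Name the randomised centre as the unit of analysis for the primary outcome, with one session count per centre.
2. Remove the correlation of 0.05 from this calculation.
3. State that SD 10 is the SD of session counts between centres.
4. Replace the requirement of 200 participants with power by number of centres. Suggested wording: With one session count per centre and a between-centre SD of 10, 80 to 160 centres give about 42% to 71% power (two-sided 5% level) for a difference of 4 sessions, and 80% power for a difference of about 6.3 sessions (80 centres) to 4.5 sessions (160 centres).

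If the authors did mean a staff-level SD, they should say so, reconcile it with the outcome definition and apply the design effect.

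The cost is rewording one paragraph and accepting a less favourable stated power. No extra recruitment is needed.

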**Methods/design:**

There are three projects in this study: The first is a pragmatic multi-centre, randomised controlled trial (RCT) of staff training, comparing CST training and outreach support with CST training only; the second, the monitoring and outreach trial, is a phase IV trial that evaluates implementation of CST in practice by staff members who have previously had the CST manual or attended training. Centres will be randomised to receive outreach support. The primary outcome measure for both of these trials is the number of CST sessions run for people with dementia. Secondary outcomes include the number of attenders at sessions, job satisfaction, dementia knowledge and attitudes, competency, barriers to change, approach to learning and a controllability of beliefs and the level of adherence. Focus groups will assess staff members’ perceptions of running CST groups and receiving outreach support. The third study involves monitoring centres running groups in their usual practice and looking at basic outcomes of cognition and quality of life for the person with dementia.

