In recent years there has been an increase in the provision of CST, with around a third of the community mental health teams in the UK reporting using it [13]. This has been facilitated by the publication of the CST ‘Making a difference’ manual and the maintenance CST manual ‘Making a difference 2’ with a CST staff-training DVD [14,15]. However, there has been little research on the long-term implementation and evaluation of CST in practice.

A recent study found that after attending a CST training course, one third of the staff went on to implement CST groups in practice [16]. All staff members felt skilled enough to run the groups; however, they identified the need for management support, regular supervision, supervision from a specialist, online forums and additional training as useful in starting and running groups. Previous research into CST has reached phase III of the MRC framework for complex interventions [7]. This research aims to study the long-term implementation of CST within two linked trials and conduct a phase IV trial that will evaluate the effects of training, and the effects of outreach support and the long-term effects of CST in practice, and will help to understand the barriers and facilitators related to implementing CST in practice.

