## Methods

### Design

This study includes three projects. The training and outreach trial and the monitoring and outreach trial differ in how staff members are recruited and in their previous exposure to training in CST. The observational study focuses on the effects of CST on people with dementia in the practice context. The three projects together will provide evidence on the most effective way of facilitating the implementation, uptake and effectiveness of the approach in a clinical context (see Table 1).

**Table 1 T1:** Project overview

**Title**	**Training and outreach trial**	**Monitoring and outreach trial**	**Observational study**
**Aim**	To assess the effectiveness of staff training and outreach support	To assess the implementation in practice of CST and outreach support	To assess the effectiveness of CST in practice
**Participants**	Dementia care staff	Dementia care staff	People with dementia
	No previous CST experience or training	Previously received CST manual/training	
**Number**	120	120	100
**Resources**	CST manual maintenance CST manual DVD	CST manual maintenance CST manual DVD	CST manual maintenance CST manual DVD
**Training**	Yes	Variable	Variable
**Outreach**	50%	50%	No
**Assessment timeframe**	Baseline, 6 and 12 months	Baseline, 6 and 12 months	Before and after CST (0, 7 or 0, 14 weeks) and maintenance CST (31 or 38 weeks)

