### Treatment as usual

Staff members within centres that are randomized to the control group deliver the CST as usual but without the additional outreach support. This can vary between centres and has the variability to change over time, but the training package offered to the intervention group will also be available to those in the control group. Therefore, the trial examines the additional effects of the outreach support.

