## Discussion

This project will pragmatically evaluate the effectiveness of staff training and outreach support by increasing the delivery of CST in practice by outreach support intervention both in new CST practitioners (TROU trial) and experienced CST practitioners (MONOU trial). The NICE-SCIE guidelines recommend CST, and this project aims to record the uptake and delivery of CST in dementia settings, to determine if it is easy to follow and replicable in practice. The MONOU trial provides a naturalistic evaluation of benefits of manual only versus manual and training in CST implementation, and both the TROU and MONOU trial will identify staff and situational factors that impede or facilitate CST implementation. One of the important advances in this study is to measure the adherence by specific questions developed in direct relation to the key principles that define CST as a therapy. It also allows the research to demonstrate, on a large scale, the knowledge, views and understanding, and approach of staff members to dementia in a variety of care settings nationwide with the secondary outcome measures. In relation to the observational study it provides an evaluation of the long-term cognitive and quality-of-life benefits of CST and maintenance CST in practice.

This study should provide definitive evidence of the effectiveness and feasibility of implementation of CST and maintenance CST in a variety of care settings. This study is likely to influence the availability, provisions and uptake of CST and maintenance CST in the UK and internationally, and may also impact on current evidence-based guidelines and policies relating to dementia care.

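### Training is randomised in neither trial, and the pooled four-group comparison partly confounds training versus manual only with trial

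*Protocol article*

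**What the plan says.** Several places present training as something the project will evaluate. Table 1 (Design) gives the TROU aim as "To assess the effectiveness of staff training and outreach support". The Background promises to "conduct a phase IV trial that will evaluate the effects of training, and the effects of outreach support". The Discussion opens with "This project will pragmatically evaluate the effectiveness of staff training and outreach support".

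The design sections describe something narrower. In TROU both arms get the training package, which is defined as usual treatment. Centres are randomised "before the training day, to receive outreach support or not", and the TROU Treatment as usual section concludes: "Therefore, the trial examines the additional effects of the outreach support". In MONOU, staff enter already holding the manual or already trained. Which of these applies is recorded before randomisation, and again only outreach is allocated.

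The Analyses section for the two trials adds, after the primary outreach comparison, a four-group comparison that draws on everyone recruited to either trial: "This will compare training and outreach support, training and no outreach support, manual only and outreach, and manual only and no outreach support". It is meant to show whether the groups differ at 6 and 12 months.

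**The concern.** A factor that both arms receive cannot be assessed by comparing those arms, so TROU says nothing about whether training works. MONOU contains trained and manual-only staff, but they were not allocated to those states. The stated aim on training therefore has no randomised comparison behind it.

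The pooled four-group comparison adds a second problem. Table 1 says that TROU staff have no previous CST experience or training, and all of them are then trained, so none can be in a manual-only group. The training groups mix newly trained TROU staff with MONOU staff trained at some earlier time, while the manual-only groups are MONOU alone. Any difference between the trials in how many sessions centres run leaks into the training contrast. The Discussion itself describes the trials as covering new and experienced practitioners, and TROU recruits at least three staff per centre against at least one in MONOU. At stake is the reading of that contrast: it could show a training difference where there is none, or hide a real one, depending on which trial runs more sessions.

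**Working it through.** **The plan's own figure.** The Analyses section gives means of 16 and 12 sessions, SD 10, alpha 0.05 and power 0.8, and states 200 participants. Per arm, n = 2 × (1.96 + 0.842)² × 10² / 4² = 98.1, rounded up to 99, or 198 in total. This reproduces the 200 as a two-sided test. It sizes outreach against control only; no figure is given for training or for the four groups.

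**Who is in each group.** Table 1 gives 120 staff per trial. Let f be the share of MONOU staff already trained (not stated, so an assumption).
- Trained: 120 + 120f. Manual only: 120(1 − f).
- TROU share of the trained group: w = 120 / (120 + 120f).

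**Bias when training has no effect.** If TROU and MONOU staff differ by g sessions on average (an assumption), and trained and manual-only MONOU staff do not differ, the pooled contrast of trained with manual only is expected to be w × g, not 0. Its sign is that of TROU minus MONOU, which the article does not let us predict.

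**Chance of a false finding.** SE = 10 × √(1/n_trained + 1/n_manual), two-sided 5% normal test, ignoring clustering and attrition. For f = 50%: SE = 10 × √(1/180 + 1/60) = 1.49, and the bias at g = 4 is 0.667 × 4 = 2.67, so bias/SE = 1.79 and the rejection probability is 43%.

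| f | Trained / manual only | w | Bias, g = 2 | Rejection, g = 2 | Bias, g = 4 | Rejection, g = 4 |
|---|---|---|---|---|---|---|
| 25% | 150 / 90 | 80% | 1.6 | 22% | 3.2 | 67% |
| 50% | 180 / 60 | 67% | 1.3 | 15% | 2.7 | 43% |
| 75% | 210 / 30 | 57% | 1.1 | 9% | 2.3 | 22% |

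Against the planned difference of 16 − 12 = 4 sessions, 2.7 is about two thirds.

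**The alternative within MONOU.** Comparing trained with manual-only staff inside MONOU removes the between-trial term. Power to detect 4 sessions (SD 10, same simplifications) is 0.48, 0.59 and 0.48 for f = 25%, 50% and 75%. At f = 50%, for example, SE = 10 × √(1/60 + 1/60) = 1.83, 4/1.83 = 2.19, and Φ(2.19 − 1.96) = 0.59. Self-selection into training remains.

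**Outreach within strata.** This stays randomised. Power for 4 sessions, with each stratum split equally between outreach and control, is 0.69, 0.77 and 0.83 among trained staff, and 0.48, 0.34 and 0.19 among manual-only staff, for the same three values of f.

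**The case against.** The strongest reply is that the design is not hidden. The Abstract names the comparator in the same sentence, "randomised controlled trial (RCT) of staff training, comparing CST training and outreach support with CST training only", and staff training and outreach support can be read as one package. The Discussion describes manual only versus manual and training in MONOU as a naturalistic evaluation. The four-group comparison is additional to a powered, randomised primary analysis. The article names no model for it, and covariates are commonly left to an analysis plan.

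Much of this stands, and it limits the importance of the point. It does not remove it. The aims in the Background and Table 1 still go beyond what is randomised, and the Analyses section fixes the population as both trials pooled, which is wider than the MONOU-only contrast that the Discussion calls naturalistic.

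Some stronger inferences are not supported:
- **The four-group comparison is the only training contrast.** The Discussion already describes one within MONOU.
- **The whole comparison is non-randomised.** Outreach against no outreach within each training stratum is randomised.
- **The bias is as large as the target effect.** With a 4-session gap between trials, that needs w = 1, meaning no trained staff in MONOU at all.
- **Supervisor arrangements separate trained from manual-only staff throughout.** The difference (research-team fallback in TROU, none in MONOU) affects only the outreach arms.
- **Manual-only staff are the ones who sought CST out.** TROU also recruits through advertisements, the commercial training day and centres with an earlier interest in CST.
- **The recruitment minimum means smaller teams in MONOU.** Its inclusion criteria match those of TROU, including at least two colleagues to run groups with.
- **A difference will be reported as caused by training.** The Analyses section makes no causal claim.

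**Conclusion.** The point holds in a limited form. Training is randomised in neither trial, so the stated aim to assess its effectiveness is not met by a randomised comparison. As specified, the pooled training versus manual-only contrast is partly, not wholly, confounded with trial.

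The size depends on two unknowns: the share of MONOU already trained and the gap between trials. With half trained, a 4-session gap and no training effect, the bias is about 2.7 sessions; across shares of 75% to 25% it runs from 2.3 to 3.2. With a 2-session gap it is 1.1 to 1.6. The mechanism follows from the text; these sizes are illustrations. The primary outreach comparison is unaffected, so this is a matter of aims and of one additional analysis.

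**What to change.** 1. Restate the TROU aim in Table 1, and the matching wording in the Background and Discussion, as the added effect of outreach on top of training.
2. In the Analyses section, replace the open four-group comparison with the randomised outreach effect within each training stratum and the outreach-by-training interaction, stratified by or adjusted for trial.
3. Estimate training versus manual only within MONOU alone, adjusted for prior CST use and centre size, and label it non-randomised, in line with the Discussion's own description.

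No new data appear to be needed: training status is recorded before MONOU randomisation, centre size is considered in forming the clusters, and prior CST use is collected by retrospective questionnaire. The cost is statistical. The MONOU-only contrast has power of about 0.5 to 0.6 for 4 sessions, before any loss to clustering or attrition. The outreach effect among manual-only staff will be imprecise, and the claim about training becomes weaker.
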